### Fidelity monitoring

To assure that the core elements that contribute to the success of intervention studies will be correctly documented and can be successfully translated into community settings, a number of process measures will be used to document, track and enhance the fidelity of this project. Firstly, all exercise supervisors will receive a written exercise protocol manual to be followed in all sessions. Secondly, participants will have their attended sessions recorded by the supervising researcher to make sure that they are receiving nearly the same amount of exercise prescription at the end of the 18 weeks of exercise intervention. Participants who have missed more than eight sessions (for being unwell or away) at the end of the 18-week period will be asked to make up these missed sessions until they reach a minimum of 35 h (out of 50 expected hours) of exercise delivery. Finally, fidelity to treatment delivery will be monitored via the use of exercise cards (per participant) for the specific training date with further details of the participant’s performance and general suggestions for the next session (i.e. improve level of certain exercise, monitor pain, watch technique, etc.).

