The “exercise park for older people” was originally introduced in Europe in 2009 as a novel purpose-built exercise park designed to improve muscular strength, flexibility, coordination and balance through active fun activities. The exercise park aims to inspire older people to be playful, to exercise, and to challenge their bodies, which can lead to a more active and healthier life style. Such indoor and outdoor exercise parks are widely available in Finland, Spain and China with only few operating in Australia. Preliminary data from The Netherlands suggests the purpose-built exercise parks may be safe and acceptable to older people. However, no evidence-based research exists that demonstrates the effectiveness of the exercise park in improving physical health, psychological well-being or independence. A report from The Netherlands [15] provided preliminary evidence of the feasibility of a 10 weeks exercise program with the exercise park equipment for a small sample of older people (*n* = 13), reporting high attendance (92 %), reduction in fear of falling and increased muscle strength and balance. Although these results are promising, further research is needed with a larger sample size and a longer intervention period to determine the effectiveness of the exercise park program on physical and psychological outcomes, well-being and independence of older adults, as well as determining the feasibility and acceptability of this type of program in the Australian community.

Therefore, the aims of this study are (1) to evaluate the effectiveness of such an exercise park in reducing the risk of falls and (2) to evaluate what other benefits, including psychosocial, functional and physiological, can be achieved by using this specific exercise park for 18 weeks with a structured and progressive program in community dwelling older adults using a randomised controlled trial design and (3) what benefits are sustained eight weeks after completion of the exercise park program.

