**Fig. 1 Fig1:**
[figure not shown]
Consort flow diagram of recruitment and randomization

Participants from the EPIG will undergo an 18-week exercise intervention. The exercise sessions will be provided two times a week (each class approximately 1 to 1.5 h duration) and will be supervised by a qualified physiotherapist or an accredited exercise physiologist. Each session will consist of 5 to 10 min warm-up exercises, followed by 45 to 75 min on the equipment stations, and will conclude with 5 to 10 min of cool down exercises. The exercise classes will include 6 to 8 participants and will be circuit-based with the warm up and cool down exercises being performed in a group and the core session being carried out in training pairs. Participants will be performing exercises that focus on strength, balance, coordination, mobility and flexibility as detailed in Tables 1, 2, 3, 4 and 5. Exercisers will be paired in stations and an exercise session can include up to eight stations (See Table 6). The intervention program will be carried out at St Bernadette’s Community Respite House, with no cost to the participants.

**Table 1 Tab1:** Strength exercises to be performed using the senior exercise park with their respective levels of progression

Exercise	Description	Functional relevance	Progressions
Push-up bar	Participant pushes body up away from the bar and brings it down towards the bar.	Strengthens arms, back and core muscles.	Standing nearly perpendicular to the bar:
			Level 1 – Wide grip.
			Level 2 – Narrow grip.
			Level 3 – Wide grip standing on a 10cm high block*.
			Level 4 – Narrow grip, standing on a 10cm high block*
			Level 6 – Narrow grip, hand release.
			Level 7 – Narrow grip, front knee tucks.
			Level 8 – Narrow grip side knee tucks.
			Level 9 - Perform the push-ups with 1 hand. Hand on shoulder line.
Modified Pull-Ups	Participant pulls body up towards the bar.	Strengthens arms, back and core muscles.	Level 1–3 – Hands narrow (undergrip), increase distance from the bar (3 distances 3 distances determined by a line on the floor).
			Level 4–6 – Hands wide (undergrip) – increase distance from the bar (3 distances)
			Level 7–9 – Hands narrow (overgrip) – increase distance from the bar (3 distances).
			Level 10–12 – Hands wide (overgrip) – increase distance from the bar (3 distances).
			If the participant reaches RPE 4/10 again, the wooden 10-cm high block can be introduced on the exercise and all levels are repeated again.

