3	Balance Stool	Calf Raises + Finger Steps
4	Sit to Stand	Rounded Snake Pipe
5	Ramp + Net + Climb Through	Sharp Snake Pipe
6	Balance Beam	Hip extension
7	Stairs	Screws / Turners
8	Step-ups	Hip Abduction

Participants in the CG will be advised to continue with their usual daily activities and will be meeting the research team every two weeks to take part in some social activities (nine meetings of two hours duration over 18 weeks of intervention). Participants from both groups will be tested at the following timelines: baseline, at the end of the intervention period (18 weeks) and two months after that (26 weeks after intervention commencement).

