### Feasibility

As the senior exercise park initiative is a new concept to the Australian older community, feasibility will be assessed and will be defined as the number of participants recruited and retained over the recruitment period, overall adherence and seasonal adherence, safety and adverse effects and number of sessions cancelled due to unfavourable weather conditions. In addition, the qualitative data collected via interviews of EPIG participants will be taken into account for feasibility purposes as they might more clearly show participants’ perceptions of this kind of initiative.

Overall adherence to the exercise program will be defined by the number of sessions attended: 100 % adherence if participant attended 35 sessions or 9 sessions of social meetings. EPIG or CG participants’ participation and attendance will be recorded via a spreadsheet diary and will be collected respectively by the exercise supervisor of that participant on each specific session or by the principal researcher. Physical activity calendars will be used to monitor if EPIG or CG participants have participated in any other physical activities during their participation in the study. Reasons for participants missing sessions will be documented on the spreadsheet diary. Participants will be given a phone call in case they miss two consecutive sessions without any communication with any exercise supervisors.

Considering that the exercise sessions are held outdoors, this study intends to investigate if the participants’ adherence would be influenced by weather conditions during the four seasons in Melbourne. Seasonal adherence will be recoded as adherence over Summer (December to end of February), Fall (March to end of May), Winter (June to end of August) and Spring (September to end of November). Also, the number of sessions that were cancelled due to rainy, windy and excessively hot days (above 37 °C) will be recorded given that these conditions would potentially put participant’s safety and health in risk.

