### Data management and statistical analysis

All analyses will be conducted on an intention-to-treat basis. If there are chance imbalances in baseline participants’ characteristics, then these variables will be used as covariates. Mixed linear modelling incorporating intervention and control groups at the baseline and two follow up time points (18 weeks and 26 weeks after intervention commencement), with the number of sessions attended and baseline physical activity level as covariates, will be carried out using SPSS. Comparisons will be made for the primary outcome (BOOMER) and secondary outcomes (functional tasks, strength measures, gait parameters, health related quality of life measures, and psychosocial measures). Although the number of falls is being recorded over a period of 12 months after the commencement of participants, this study is not powered for falls outcomes. Regarding the qualitative data being collected, the interviews from EPIG participants will be analysed using a thematic analysis approach [55], as described above.

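### Make-up sessions fall after week 18 in the exercise arm only, so for those who take them the week-26 visit comes less than the eight weeks after completion stated in aim 3

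*Protocol article*

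**What the plan says.** The protocol article fixes the programme length under Recruitment and randomization: "Participants from the EPIG will undergo an 18-week exercise intervention". There are two classes a week, "each class approximately 1 to 1.5 h duration". The same section places the follow-up visits "at the end of the intervention period (18 weeks) and two months after that (26 weeks after intervention commencement", and Data management and statistical analysis models the same "two follow up time points (18 weeks and 26 weeks after intervention commencement". Aim 3, at the end of the Background, asks "what benefits are sustained eight weeks after completion of the exercise park program".

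Fidelity monitoring adds a rule for poor attenders. Those who missed more than eight sessions "at the end of the 18-week period will be asked to make up these missed sessions". The floor is given in hours: they are to "make up these missed sessions until they reach a minimum of 35 h (out of 50 expected hours) of exercise delivery". The rule is about hours of exercise. Controls have nine two-hour social meetings, 18 hours in all, and no make-up rule is stated for them.

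**The concern.** A shortfall counted at the end of week 18 can only be made good after week 18. For anyone who does so, three statements cannot all be true: the programme ends at week 18, the last visit is at week 26, and that visit is eight weeks after completion.

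At stake is the reading of aim 3. The week-26 score is meant to show what survives eight weeks without supervised exercise. For these participants part of the training falls between the two follow-up visits and the time off is shorter, in one arm only. If benefits fade, the exercise mean at week 26 is higher than it would be after a true eight-week gap.

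The rule also defeats its own purpose. It is meant to bring participants to a similar amount of exercise by the end of the 18 weeks, but hours delivered after the week-18 visit cannot contribute to the result measured there.

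The planned covariate does not repair this. The model adjusts for the number of sessions attended, not for when they took place. With 75-minute classes, a participant who reached 28 sessions by week 18 and one who reached 28 at week 23 would have the same value, if make-up sessions are counted at all.

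**Working it through.** **Plan's own interval.** 26 − 18 = 8 weeks. This agrees with aim 3 for everyone whose programme ends at week 18.

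**Inputs from the article.** Two classes a week for 18 weeks (Recruitment and randomization): 2 × 18 = 36 sessions. Class length 1 to 1.5 h, so 36 to 54 h in total, and 36 × 1.25 = 45 h at the 75-minute midpoint. Trigger: more than 8 missed. Floor: 35 h of 50 (Fidelity monitoring). Fifty hours over 36 sessions implies 50/36 = 1.39 h, about 83 minutes.

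**Assumptions.** Make-up runs at the usual two classes a week, and every session owed is taken.

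**Formulas.** Sessions needed = 35 h ÷ class length, rounded up. Sessions owed = sessions needed − (36 − missed), not below 0, and only if more than 8 were missed. Overrun in weeks = owed ÷ 2. Gap to week 26 = 8 − overrun.

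| Class length | Sessions for 35 h | Missed 9: owed, gap | Missed 12: owed, gap | Missed 18: owed, gap |
|---|---|---|---|---|
| 60 min | 35 | 8, 4 wk | 11, 2.5 wk | 17, −0.5 wk |
| 75 min | 28 | 1, 7.5 wk | 4, 6 wk | 10, 3 wk |
| 83 min | 26 | 0, 8 wk | 2, 7 wk | 8, 4 wk |
| 90 min | 24 | 0, 8 wk | 0, 8 wk | 6, 5 wk |

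Worked line: at 75 minutes with 18 missed, 18 were attended (22.5 h). 28 − 18 = 10 are owed, which takes 10/2 = 5 weeks and leaves 8 − 5 = 3 weeks. The negative entry means that make-up would run past the week-26 visit.

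**Where make-up starts.** At 60 and 75 minutes it starts at 9 missed. At 83 minutes it starts at 11 missed: 25 attended, 1 owed, gap 7.5 weeks. At 90 minutes it starts at 13 missed: 23 attended, 1 owed.

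**Why the unit matters.** The trigger is in sessions and the floor in hours. They agree at 75 minutes, where missing 8 leaves 28 × 1.25 = 35 h. At 60 minutes, missing 8 leaves 28 h, below the floor, yet triggers nothing. At 83 minutes, missing 9 leaves 27 × 1.39 = 37.5 h, so the trigger is met but nothing is owed.

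**Sensitivity to the session count.** Feasibility sets full "adherence if participant attended 35 sessions or 9 sessions of social meetings", that is 35 rather than 36. With 35 scheduled, the 75-minute gaps for 9 and 18 missed become 7 and 2.5 weeks, half a week shorter.

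In every case where at least one make-up session is taken after week 18, the gap is below eight weeks, whatever the class length.

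**The case against.** **No figure is wrong.** This is correct: 26 − 18 is 8. The point is an internal inconsistency between a rule and a visit schedule, not an arithmetic error.

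**The between-group contrast stays valid.** Under intention to treat, make-up can be seen as part of the assigned programme, and both arms are compared at the same time from the start. This stands. What fails is the description of that contrast as the benefit left eight weeks after completion.

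**Make-up may be meant to fall inside the 18 weeks.** The sentence before the rule speaks of near-equal exercise by the end of that period. That supports the intention, but the rule itself counts absences when the 18 weeks are over, and no wording moves it earlier.

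**Operational detail belongs elsewhere.** Visit windows and latest dates are commonly left to a full protocol or to the supervisors' manual, and their absence would be no finding. Here, however, the article states a rule that conflicts with its own definition of the last visit.

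**Visits might be deferred.** A reader might infer that the visits wait for make-up, so that the arms are measured at different times under one label and the week-18 comparison is distorted. The documents do not support this. The abstract, Design and setting, Recruitment and randomization, and the analysis section all fix follow-up at 18 and 26 weeks, and nothing lets a visit move.

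**Uptake is unknown.** Participants are only asked to make up sessions. This stands, and it limits what can be said about size.

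**Conclusion.** The inconsistency is real and should be corrected. It concerns aim 3 at week 26, for an unknown number of poor attenders in the exercise arm. For each of them the week-18 visit precedes the end of the programme and the week-26 visit comes less than eight weeks after it. The bias overstates sustained benefit only if benefits fade.

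A reader might take 3 to 7.5 weeks as the range the plan produces. It is not. Those figures assume 75-minute classes, two make-up classes a week, full uptake, and 9 to 18 missed sessions. Longer classes shrink the overrun, and shorter classes or more absences enlarge it. A reader might also want the effect in BOOMER points. The article gives neither a rate of fading, nor the benefit in poor attenders, nor the share affected, so no such figure is supported.

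With visits held at weeks 18 and 26, the week-18 BOOMER result is unaffected, because later sessions cannot change a score already taken. The sample size does not depend on this point.

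**What to change.** Check attendance during the programme, for example at week 12, and offer make-up sessions only within the 18 weeks, with none after the week-18 visit. Keep both visits at weeks 18 and 26 from the start in both arms. State the trigger and the minimum in one unit, either sessions or hours.

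If later make-up is kept, set a latest date for it. Then add a 26-week sensitivity analysis by time since the last session. The session dates needed are already recorded on the dated exercise cards and in the attendance diary.

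The cost is a few sentences in the protocol and the supervisors' manual and one attendance check, with no extra visits. The downside is that some poor attenders, especially those unwell or away late in the programme, will finish with fewer than 35 hours. With fixed visits, however, hours delivered after week 18 could not have contributed to the week-18 result.

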### Sample size

Power analysis was undertaken using previously published discharge data on the primary outcome measure - the BOOMER balance measure [26], and assuming an improvement of 3 points (reported as the minimum detectable difference [26]) and an effect size of 0.5. A sample size of 48 participants per group will be required for a power of 0.80 and alpha of 0.05. We will allow for 20 % dropout rate (this is a conservative estimate based on previous exercise programs with older people), and therefore will recruit 60 participants per group.

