### Recruitment and randomization

Participants will be recruited from Melbourne suburbs. Local senior organizations, retirement villages, community centres, senior clubs and associations in the areas around the park location will be contacted for recruitment purposes. Participants will be also recruited via community health promotion events and advertisement in local newspapers, magazines and online social networking media. Participants will be informed about the project by posters placed in healthcare facilities and places with high circulation of senior citizens and mail-out advertisements to health care practitioners in Melbourne. Participants will be randomly allocated to one of the following groups: (1) Exercise Park Intervention Group (EPIG) or (2) Control Group (CG). Block randomization stratification by gender will be undertaken, so that blocks of 12 participants will be recruited at a time, randomized into one control group of six participants and one exercise groups of six participants (Fig. 1). To accommodate couples (e.g. partners/married couples) participation, randomisation by couple will also take place. Assessors will prepare the envelopes with six paper codes (three exercise intervention and three control group) which will be added to opaque not concealed envelopes. There will be three envelopes: one for couples, one for females and one for males. Participants will be asked to pick one paper from their respective envelope and the picked paper will assign the participant to either the exercise intervention group or control group. Recruitment will be undertaken over a period of 14 months to achieve a sample size of 60 participants in each group. Assessors and participants will not be blinded to their respective group allocation (EPIG or CG).

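### The printed sample size inputs (effect size 0.5, power 0.80, alpha 0.05) give 64 per group for an unadjusted two-sided comparison, not 48; the 80% power rests on an assumption that is not stated

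*Protocol article*

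**What the plan says.** The Sample size section bases the calculation on published discharge data for BOOMER. It assumes a 3-point improvement, described as the minimum detectable difference, "and an effect size of 0.5". It then states: "A sample size of 48 participants per group will be required for a power of 0.80 and alpha of 0.05". On attrition it says "We will allow for 20 % dropout rate", and Recruitment and randomization sets out "to achieve a sample size of 60 participants in each group".

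The section names no test, no sidedness, no SD and no correlation between repeated measurements. The analysis appears under Data management and statistical analysis: "Mixed linear modelling incorporating intervention and control groups at the baseline and two follow up time points". The covariates named there are sessions attended and baseline physical activity. Other baseline characteristics enter only if they are imbalanced by chance. The sample size section does not say that this model was used to derive 48.

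**The concern.** Effect size, power, alpha and group size are tied together by a standard formula, so a printed set of all four can be checked. Read in the usual way (two independent groups, two-sided 5%, no adjustment), this set does not agree: 48 is about a quarter below the number required.

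BOOMER is the only primary outcome and this is the trial's only power statement. A null result would be read against the stated 80%. If the calculation was the conventional one, that reading credits the trial with more sensitivity than it has. If it was a different one, readers cannot tell which, and cannot judge whether its hidden assumption is reasonable.

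**Working it through.** **Inputs.** From Sample size: d = 0.5, power 0.80, alpha 0.05, 48 per group, 20% dropout. From Recruitment and randomization: 1:1 allocation, 60 per group. Sidedness, test and correlation r are not given, so each is varied below.

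**1. The part that reproduces.** Dropout inflation: 48 / (1 − 0.20) = 60 per group. This is correct.

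**2. Unadjusted, two-sided 5%.** By normal approximation, n = 2 × ((1.96 + 0.842) / 0.5)² = 62.8, so 63 per group. The noncentral t gives 63.8, so 64. Neither is 48.

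**3. Unadjusted, one-sided 5%.** n = 2 × ((1.645 + 0.842) / 0.5)² = 49.5, so 50. The noncentral t gives 50.2, so 51. This is close to 48 but does not produce it.

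**4. Power for the unadjusted test at d = 0.5 (noncentral t).**

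| Evaluable per group | Two-sided 5% | One-sided 5% |
|---|---|---|
| 48 | 0.679 | 0.784 |
| 60 (no dropout) | 0.775 | 0.859 |
| 64 | 0.801 | 0.879 |

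**5. Effect that 48 per group can detect.** With power 0.80 and two-sided 5%, d = 0.578. If 3 points and 0.5 describe the same contrast, the implied SD is 3 / 0.5 = 6, and 0.578 × 6 is about 3.5 points. Equivalently, 3 points would need an SD of 3 / 0.578, about 5.2.

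**6. Baseline-adjusted analysis (ANCOVA or a model that constrains the baseline means to be equal), two-sided 5%.** The variance is multiplied by 1 − r², so the effective effect size is 0.5 / √(1 − r²).

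| Assumed r | 1 − r² | Effective d | Power at 48 per group |
|---|---|---|---|
| 0.3 | 0.91 | 0.524 | 0.72 |
| 0.5 | 0.75 | 0.577 | 0.80 |
| 0.7 | 0.51 | 0.700 | 0.92 |

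At r = 0.5 the required number is 63.8 × 0.75 = 47.8, so 48.

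**7. Difference in change, baseline group means left free, two-sided 5%.** The variance is multiplied by 2(1 − r). At r = 0.5 the factor is 1, so nothing is gained and power at 48 stays at 0.679. To match the factor of 0.75 in step 6, 2(1 − r) = 0.75 gives r = 0.625. At r = 0.3 the factor is 1.4 and power at 48 falls to 0.54.

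**The case against.** The strongest defence is that the 0.68 describes an analysis the protocol does not plan. The planned model uses baseline and two follow-ups, and step 6 lands on 48 exactly at an ordinary correlation of 0.5. That suggests an unstated assumption as readily as a slip. Power could be higher still. If the contrast were the baseline-adjusted mean of both follow-ups, with equal correlations r and d = 0.5 at both times, the variance factor is (1 + r)/2 − r². This is at most 0.5625, reached at r = 0.25, and power at 48 is then about 0.90 or more for r from 0 to 0.7. The SD and correlation may also stand in the cited BOOMER source or in a fuller protocol, and a journal article condenses.

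Much of this stands. A reader might infer that 48 per group cannot give 80% power, or that a true 0.5 SD effect would be missed about one time in three. The document does not support either as a flat statement, because it fixes neither the test nor the contrast, and power under the planned model cannot be determined from it. Nor can clustering from randomising couples or training in classes be counted against the figure: no intraclass correlation or expected number of couples is given.

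The defence does not rescue the sentence as printed. The article gives its inputs and its result together, so this is more than a detail left to another document. The stated source is discharge data, with no mention of a baseline correlation, and baseline BOOMER is not listed as a covariate but is one of the modelled time points. Whether r = 0.5 suffices therefore depends on a model form that is also unstated (step 7). The one-sided reading has no support in the text and still falls short of 48.

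**Conclusion.** The point holds in a conditional form. From the printed inputs, an unadjusted comparison does not give 48 per group: it needs 64 two-sided or 51 one-sided. Power at 48 is then 0.68 or 0.78 respectively, against a stated 0.80, and recruiting 60 with no losses would give 0.78 two-sided. The stated power is recovered two-sided under baseline adjustment with r of about 0.5, or with r of about 0.625 for an unconstrained difference in change. Neither the correlation nor the model form is given, so the 80% is unsupported as written.

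These results assume equal groups, a common SD and 0.5 read as a standardised mean difference. The conversion to 3.5 points also assumes that the 3 points and the 0.5 refer to the same contrast. The finding concerns the power statement. It does not show that the trial is underpowered for its planned analysis, and it is not a case for enrolling more participants.

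**What to change.** Rewrite the sample size paragraph in one of two ways and leave recruitment at 60 per group.

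- **Option A, unadjusted.** State that with 48 evaluable per group, power is 0.68 for d = 0.5 and 0.80 for d = 0.58, at two-sided 5% without baseline adjustment.
- **Option B, planned model.** Base the statement on the baseline-adjusted BOOMER difference at 18 weeks and name the model form (constrained baseline or ANCOVA). Give the two-sided alpha, the SD behind equating 3 points with 0.5 SD, and the assumed correlation with its source. Show power at 48 per group of 0.72, 0.80 and 0.92 for r = 0.3, 0.5 and 0.7. The analysis section must then specify that same contrast, because a correlation of 0.5 is not enough if baseline group means are left free.

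The cost is one reworded paragraph, plus a clause in the analysis section under option B. The power statement becomes less favourable under A, or carries an explicit assumption under B.
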